### Sample size

With a confidence level of 95% and a test power of 80%, the number of samples required for each group (intervention and control) is determined based on study conducted by Rostami et al. [42]. The required number of samples is estimated 55 per each group. Considering a 10% drop out, a sample of 60 participants per each group will be included.

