
Data will be collected using the study measures. The outcomes will be assessed in four points in time: before, immediately, 3, and 6 months after the interventions. Questionnaires of behavior and health belief model are measured with a 5-point Likert scale from completely disagree to completely agree.

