### Data analysis

To conduct statistical analysis of data, the IBM SPSS Modeler version 21 will be used. Descriptive statistics such as frequency and percentage, mean, and standard deviation will be used. For classification variables, chi-square and Fisher’s exact tests will be used to determine the difference between groups. Before and after evaluation, intra-group comparisons are determined by paired *t*-test. Independent group means will be evaluated with a 95% confidence interval. The Kolmogorov-Smirnov test will be used to check the normality of data. Finally, after adjusting for gender and age group, a multivariable linear regression model will be used to examine the combined effects of vitamin physiotherapy and social-psychological interventions on changes in pain scores. Repeated measure analysis of variance will also be used. This study will use exploratory factor analysis to identify the underlying categories of an item set.

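### Repeated-measures ANOVA, the only named method that uses all four visits together, in its standard form keeps only residents seen at every visit; a mixed model would use all observed VAS values

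*Protocol article*

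**What the plan says.** The Outcome measures section sets the schedule: "The outcomes will be assessed in four points in time: before, immediately, 3, and 6 months after the interventions". The Data analysis section names several methods for these data:

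- within groups, "Before and after evaluation, intra-group comparisons are determined by paired" t-tests;
- between groups, a comparison of means with a 95% confidence interval;
- a regression that adjusts for age group and gender: "a multivariable linear regression model will be used to examine the combined effects of vitamin physiotherapy and social-psychological interventions on changes in pain scores";
- finally, "Repeated measure analysis of variance will also be used".

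None of these is called primary. For the repeated-measures ANOVA the article gives no outcome, factors or rule for missed visits.

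The Sample size section starts from "With a confidence level of 95% and a test power of 80" per cent, states that "The required number of samples is estimated 55 per each group", and then allows for losses: "Considering a 10% drop out, a sample of 60 participants per each group will be included".

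**The concern.** A repeated-measures ANOVA of the classical kind needs one complete row per resident. A resident with VAS at baseline, straight after the programme and at 3 months, but not at 6 months, contributes nothing to it unless values are imputed beforehand. The plan itself expects losses. It follows nursing-home residents with pain until 6 months after the intervention.

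Any arm-by-time result for pain would have to come from this analysis, because no other listed method uses all four visits jointly. At stake are the precision of that result and whether it describes the enrolled residents or only those who completed every visit.

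Arm-dependent loss is plausible from the design. The intervention arm is asked to attend 8 × 3 × 1 h = 24 h of posture sessions and 8 × 2 × 1.5 h = 24 h of psychological sessions, 48 h in all, plus daily walking and tablets. Controls receive nothing until the 6-month questionnaire is done.

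**Working it through.** **Inputs from the protocol article.** 55 evaluable and 60 enrolled per group, 10% drop-out, 95% confidence, 80% power (Sample size); one baseline and three follow-up assessments (Outcome measures). **Assumed:** a two-sided 5% test. The difference and SD behind the 55 are not given, so the effect size is back-calculated.

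1. *The plan's own inflation.* 55 / 0.90 = 61.1, rounded up to 62; 55 × 1.10 = 60.5, rounded up to 61. The stated 60 is within two residents of either.

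2. *Implied effect size.* d = √(2/55) × (1.960 + 0.842) = 0.534 SD.

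3. *Loss at the planned drop-out.* If 10% of residents have any missed visit, 120 × 0.10 = 12 are dropped and 60 × 0.90 = 54 per arm remain. Power = Φ(0.534 × √(54/2) − 1.960) = Φ(0.816) = 79.3%.

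4. *Loss if visits are also missed intermittently.* With a proportion m missed independently at each of three follow-ups, complete cases are 60 × (1 − m)³ per arm. The rates are assumptions.

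| Missed per visit | Complete per arm | Dropped of 120 | Power |
|---|---|---|---|
| 5% | 51.4 | 17.1 | 77.3% |
| 10% | 43.7 | 32.5 | 70.5% |

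5. *Bias.* An illustrative simulation used 60 per arm, four visits, SD 2, correlation 0.5, permanent drop-out at the 3- and 6-month visits and 3,000 runs. The true month-6 difference was −1.068 (0.534 × 2). It compares complete cases with an estimate that uses every observed visit. Apart from the arm size and the number of visits, the settings are assumed or back-calculated.

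| Missingness | Complete | Complete cases | All observed visits |
|---|---|---|---|
| Completely at random | 81% | −1.070 (SE 0.405) | −1.069 (SE 0.386) |
| More likely after higher pain, both arms | 86% | −0.999 | −1.070 |
| After higher pain in controls, after lower pain in the intervention arm | 82.5% | −0.688 | −1.065 |

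Pure chance loss costs a little precision and causes no bias. A mechanism common to both arms moves the estimate by about 0.07 points. Opposite mechanisms move it by about 0.38 of 1.07 points. In both non-random settings the shift was toward no effect.

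The power figures and the simulation ignore clustering by home. The table in step 4 shows lost numbers only: independent random misses of that kind would not bias the estimate.

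**The case against.** The article never says that residents with a missed visit will be removed. That follows from the standard form of the method, and imputation beforehand is not ruled out. Rules for missing data are commonly left to an analysis plan, so their absence is not at issue here. The ANOVA is also an additional analysis: a change-score regression needs two pain values and not four, so a resident with an incomplete series is not lost to every analysis. The 10% allowance nearly covers a complete-case loss of the same size, and corrections for non-sphericity exist. All of this stands.

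A reader might go further and infer that the plan biases the trial's result, probably in favour of the intervention. The documents do not support that. They say nothing about why visits will be missed, complete-case analysis is unbiased if values are missing completely at random, and the non-random settings tried above moved the estimate the other way. A reader might also infer that all 12 expected drop-outs have usable follow-up values. Some may have baseline only, and the mixed model proposed below would not use those either.

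The objection does not remove the point that the one joint analysis of the four visits is a named method that copes poorly with the losses the plan itself expects.

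**Conclusion.** The point holds as a weakness of a stated method, with a modest expected size. At the planned 10% drop-out, the repeated-measures ANOVA would leave out about 12 of 120 residents and have about 79% power instead of 80%. The loss becomes material only with intermittent misses on top, at about 70% power if 10% are missed per follow-up visit. Bias is a risk of unknown direction: none under completely random loss, small in the common-mechanism example, and appreciable if reasons for loss differ by arm.

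This rests on the standard complete-case form of the method, a two-sided test, the back-calculated d of 0.534, the assumed rates of missed visits, and no allowance for clustering. It is a reason to change the method before analysis. It does not show that the results will be wrong.

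**What to change.** In the Data analysis section, replace the repeated-measures ANOVA for VAS with a linear mixed model fitted to all observed follow-up visits:

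- fixed effects for arm, visit (categorical), arm × visit and baseline VAS;
- unstructured within-person covariance;
- a random effect for nursing home;
- a small-sample degrees-of-freedom correction such as Kenward-Roger.

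Report the arm difference with its interval at each follow-up visit from this one model. The correction is needed because the Sampling section implies only 4 areas × 2 homes = 8 homes, four per arm (4 × 15 = 60 residents).

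The cost is a change of analysis wording and slightly more analysis work, with no extra visits or residents. The plan says "the IBM SPSS Modeler version 21 will be used", so confirm that this software can fit the model with the correction. The model relies on data being missing at random, which cannot be verified from the observed data. Intervals will be wider once home is included.

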**Methods:**

This is a parallel randomized clinical trial among elderly people aged 60 years and over living in a nursing home who suffer from musculoskeletal pain. Eligible participants will be divided into two groups including the intervention group who will receive a multidisciplinary intervention (vitamin D consumption, psycho-social stress management, and physiotherapy) and the control group who will receive usual care. Data collection instruments will include demographic data, the Depression, Anxiety, and Stress Scale (DASS), the visual analogue scale (VAS), and a self-designed questionnaire containing the HBM constructs. The interventions will be carried out by the educational team (general practitioner, psychologist, physiotherapist, and health education specialist). Interventions include changing the wrong beliefs of the elderly, taking 800 units of vitamin D daily, daily walking exercise by the elderly for at least 30 min and maintaining proper body posture during daily activities, muscle relaxation, relaxation techniques, regular exercise, examining their diet and eliminating stimulants (such as smoking and coffee), regular visits with friends and family, and deep breathing techniques. All questionnaires will be completed by the elderly before, after, 3, and 6 months after the intervention.

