### Outcomes

The primary outcome of this study is to reduce musculoskeletal pain in the elderly. The secondary outcomes would be reduction in psychological distress (depression, anxiety, and stress) and improvements in beliefs among elderly using the health belief model constructs.

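### In the usual four-visit layout, the repeated-measures ANOVA gives no direct estimate of the pain reduction; baseline VAS pain is better entered as a covariate

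*Protocol article*

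**What the plan says.** The Outcomes section gives the target: "The primary outcome of this study is to reduce musculoskeletal pain in the elderly". Under Outcome measures, pain is scored on a 0 to 10 VAS, and the timing is given as "The outcomes will be assessed in four points in time: before, immediately, 3, and 6 months after the interventions".

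The Data analysis section names these methods that could bear on pain:

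- a within-arm comparison, where "intra-group comparisons are determined by paired" *t*-test;
- independent group means with a 95% confidence interval, with no visit named;
- a regression on changes in pain scores: "after adjusting for gender and age group, a multivariable linear regression model will be used to examine the combined effects" of the intervention components;
- and then "Repeated measure analysis of variance will also be used".

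The repeated-measures sentence does not give the levels of the visit factor, any covariates, or which effect carries the conclusion. Gender and age group are the only adjustment variables named, and they belong to the regression. Baseline pain is not a covariate in any analysis. It enters only through change scores and before-after comparisons.

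**The concern.** Repeated-measures ANOVA is the only named method built for several follow-up visits at once. Applied in its default form to the four stated visits, it puts the pre-intervention score on the outcome side, although treatment cannot yet have had an effect at that visit. The output is then three tests:

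- **Group:** averages the arm difference over all four visits, including the one where it is expected to be zero.
- **Time:** describes change averaged over both arms and says nothing about treatment.
- **Group by time:** asks whether the two profiles are parallel. It is a proper test of differential change, but it returns neither size nor direction.

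None of these is the between-arm difference in pain after the intervention, even with complete data. A reader who takes the group line as the treatment effect gets a diluted figure. A reader who takes the interaction gets a p-value that still needs a contrast. Meanwhile the baseline VAS score, which is already collected and likely to predict later pain, is not used to sharpen the comparison.

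**Working it through.** **Inputs from the protocol.** Two groups, and four visits of which one is before the intervention (Outcome measures). Sample size uses 95% confidence and 80% power: "The required number of samples is estimated 55 per each group". Sampling draws one intervention and one control home per area in four areas, 15 residents each, so 4 × 15 = 60 per group after the dropout allowance.

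**The plan's own figure.** The 55 cannot be recomputed, because no difference or SD is given. Solved backwards (two-sided 5%, 80% power), it implies d = (1.960 + 0.842) × √(2/55) = 0.534 SD by the normal formula, or 0.539 SD with the *t* distribution. I use 0.539. This is an assumption about the effect, not a value the protocol states.

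**Further assumptions.** A constant effect d at all three post-intervention visits, equal expected baselines, SD 1 at each visit, equal correlation r between any two visits, n = 55 per group, and residents independent.

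**Dilution of the group effect.** Let the arm differences at the four visits be (b, D1, D2, D3), with b the chance difference at baseline. The group main effect estimates (b + D1 + D2 + D3)/4 = ¾ × mean(D1, D2, D3) + ¼ × b. With b = 0 the factor ¾ is exact for any follow-up profile. With a constant effect it is 0.75 × 0.539 = 0.404 SD, a quarter below 0.539.

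**Interaction.** Degrees of freedom are (2 − 1)(4 − 1) = 3. The squared deviations of (0, d, d, d) from their mean sum to (0.75² + 3 × 0.25²)d² = 0.75d² = 0.218. The noncentrality is (55/2) × 0.218/(1 − r), which is 8.6, 12.0 and 20.0 at r = 0.3, 0.5 and 0.7. The reference is the noncentral F with 3 and 324 df.

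**Variance of each single-df quantity, per person:**

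| Quantity | Formula | r = 0.3 | r = 0.5 | r = 0.7 |
|---|---|---|---|---|
| Four-visit mean | (1 + 3r)/4 | 0.475 | 0.625 | 0.775 |
| Post mean minus baseline | (1 + 2r)/3 + 1 − 2r | 0.933 | 0.667 | 0.400 |
| Post mean, baseline as covariate | (1 + 2r)/3 − r² | 0.443 | 0.417 | 0.310 |

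For these, the noncentrality is (55/2) × effect²/variance.

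**Power:**

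| Analysis | Estimates | r = 0.3 | r = 0.5 | r = 0.7 |
|---|---|---|---|---|
| Group main effect, four visits | 0.404 | 86% | 76% | 67% |
| Group by time, 3 df | no single estimate | 68% | 83% | 97% |
| 1-df contrast, post mean minus baseline | 0.539 | 83% | 93% | 99% |
| Post mean, baseline as covariate | 0.539 | 99% | 99% | 99.9% |

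**Sensitivity to the constant effect.** Take a fading profile of 0.534, 0.356 and 0.178 SD at r = 0.5. The average post-intervention effect is 0.356 and the four-visit group effect is 0.267, again three quarters. Power is 43% (group), 69% (interaction), 63% (1-df contrast) and 83% (baseline as covariate). The covariate form stays ahead, but the interaction now beats the simple change contrast.

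**The case against.** The strongest reply is that the protocol does not say the pre-intervention score is an outcome level. Outcome measures states when data are collected, not what enters the model, and three post-intervention visits with a baseline covariate would also fit the repeated-measures sentence. Levels and contrasts are commonly left to an analysis plan. This stands. A reader might infer that the plan as written understates the effect by 25%, and the text does not support that. The default layout is still the more natural reading: the pre-intervention visit is listed among the four outcome assessments, the method named is analysis of variance, and baseline pain appears nowhere as a covariate.

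Second, nothing says the group or time main effect will be read as efficacy. Group by time is a legitimate test of differential change, and the same model can yield contrasts. This also stands. The 1-df contrast keeps baseline as a level and still reaches 83/93/99%, so much of the gap in the table comes from which effect is read and from covariate adjustment, not from baseline being a level as such.

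Third, the ANOVA is an additional analysis, beside group means with confidence intervals and a change-score regression that can address pain reduction. A reader might infer that the trial depends on the ANOVA for its result, and the document does not say so. The reply is only partial, however. Neither alternative names a visit, the regression sentence states no arm term, and neither adjusts for baseline as a covariate.

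Finally, the powers rest on a back-solved effect and ignore clustering. They compare analyses with one another and do not describe this trial's actual power.

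**Conclusion.** The point holds as a conditional one. If the four stated visits form the repeated factor, the group effect is exactly three quarters of the average post-intervention difference (given equal expected baselines), and the interaction is a valid 3-df test without a single estimate. With only four homes per arm, a chance baseline difference is plausible, and a quarter of it would pass directly into the four-visit group effect, in either direction. The document does not establish that this layout is intended or that the wrong line will be read, so no certain bias can be charged to the plan.

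What remains whichever layout is intended is that baseline VAS is collected and adjusted for nowhere. Using it as a covariate gives a directly interpretable arm difference with about 99% power in the constant-effect illustration, against 67 to 86% for the four-visit group effect and 68 to 97% for the interaction. The ordering is informative; the levels are not, because they assume 0.54 SD, equal correlations and independent residents, and will fall once homes are accounted for. This is a modest improvement worth making, not a fatal flaw.

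**What to change.** In the Data analysis section, replace the repeated-measures sentence with one that:

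1. takes the VAS scores at the three post-intervention visits as the repeated outcomes;
2. enters the pre-intervention VAS score as a covariate;
3. names the arm difference over those three visits, with its 95% confidence interval, as the result read from this model;
4. states that neither the time main effect nor a group effect that includes the pre-intervention visit will be presented as evidence of efficacy.

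If this is already the intention, that sentence settles the matter. The cost is analysis wording only: the baseline score is already collected, and no visit, participant or measurement is added. The same model will need to account for nursing home, which this change does not do.

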### Dissemination policy

Trial results will be submitted to peer-reviewed journals for publication. Part of the data, such as information regarding the main outcome, can be shared.

## Discussion

This study aims to design a multidisciplinary educational intervention based on health belief model (HBM) for elderly residents of nursing home. One of the features of this study is its focus on improving the health of elderly residents in nursing homes. Considering that elderly suffer from various diseases such as musculoskeletal pain, the main purpose of this study was to design a multimodal intervention based on HBM to obtain preventive behaviors of musculoskeletal pain in the elderly. The positive effect of interventions on teachers [47] as well as combined programs (supplement consumption and physical activity) based on HBM [48] has been proven. Various studies have also confirmed the positive effect of HBM-based interventions [49, 50] and the effect of multimodal interventions on reducing pain in the elderly [51]. The current study might provide similar findings. Different programs have been designed in various countries to reduce musculoskeletal pain, such as the multidisciplinary rehabilitation programs in Germany that aim to improve the performance and workability of individuals [52, 53]. In the USA, the National Institute of Health has allocated a budget for musculoskeletal conditions [3]. Routine care is provided for the elderly in healthcare centers in Iran, but there is no specific care for preventing and controlling musculoskeletal disorders, and in elderly care centers may not be provided due to lack of compliance with health standards [54]. Even in the interventional researches that are done on the elderly population, the elderly group living in the nursing home is eliminated [55]. Also, in most research related to physical activity, the elderly is left out due to age-related diseases [56]. Therefore, the strengths of this study we can mention the combined intervention to reduce musculoskeletal pain in the elderly living in nursing homes and the group interaction of the elderly in the intervention group, which reduces stress and follows the educational program. Also, sampling from several centers and the presence of a control group that only receive routine interventions are other strengths of this study, because the elderly care status can be improved if the results of this study will be positive.

### Limitations

Among the limitations of this study is the inability to control the conditions of the nursing home, and the elderly may have difficulty interpreting their pain when using the VAS scale. Self-reporting of information is another limitation of this study.

## Data Availability

Non-applicable participant level data will not be shared.

## Abbreviations

MSDs: Musculoskeletal disorders
HBM: Health belief model
DASS: Depression, Anxiety, and Stress Scale
VAS: Visual analogue scale
CVI: Content validity index
CVR: Content validity ratio
